## Abstract

**Introduction:**

Anorexia nervosa (AN) is a debilitating and potentially chronic eating disorder, characterized by low hedonic drive toward food, which has been linked with perturbations in both reward processing and dopaminergic activity. Neuromelanin‐sensitive magnetic resonance imaging (MRI) is an emerging method to index midbrain neuromelanin—a by‐product of dopaminergic synthesis. The assessment of midbrain neuromelanin, and its association with AN psychopathology and reward‐related processes, may provide critical insights into reward circuit function in AN.

**Methods:**

This study will incorporate neuromelanin‐sensitive MRI into an existing study of appetitive conditioning in those with AN. Specifically, those with acute and underweight AN (*N* = 30), those with weight‐restored AN (*N* = 30), and age‐matched healthy controls (*N* = 30) will undergo clinical assessment of current and previous psychopathology, in addition to structural neuromelanin‐sensitive MRI, diffusion MRI, and functional MRI (fMRI) during appetitive conditioning.

**Conclusion:**

This study will be among the first to interrogate midbrain neuromelanin in AN—a disorder characterized by altered dopaminergic activity. Results will help establish whether abnormalities in the midbrain synthesis of dopamine are evident in those with AN and are associated with symptomatic behavior and reduced ability to experience pleasure and reward.

## INTRODUCTION

1

Anorexia nervosa (AN) is a debilitating and potentially life‐threatening eating disorder that yields mortality rates among the highest of any psychiatric illness, with a crude mortality rate of 5.6% (Arcelus et al., 2011). While the benefits of specialized treatments remain limited (Murray et al., 2019), AN may run a chronic and relapsing illness course, with more than half of those afflicted with AN still meeting diagnostic criteria more than two decades after illness onset (Fichter et al., 2017). Moreover, AN has been associated with multisystemic organ damage, bone disease, and structural and functional brain impairment (Mitchell & Crow, 2006), which cumulatively render functional impairments comparable to those seen in schizophrenia (Vos & Mathers, 2000) and autism (Whiteford et al., 2015). Upon the backdrop of risk associated with AN, and the modest rates of treatment response, the need to elucidate the brain‐based mechanisms of AN is critical so that precision treatments can be developed (Schmidt & Campbell, 2013).

Symptomatically, AN is characterized by self‐imposed starvation, emaciation, an intense fear of weight gain, and a marked disturbance in the perception of one's body shape and weight (American Psychiatric Association, 2013). Behaviorally, this typically manifests as an avoidance of palatable foods, despite their near universal hedonic properties in individuals without AN (Kringelbach, 2004). In exploring the mechanisms of this pervasive food restriction, a growing body of evidence has indicated aberrant experiences of reward among those with AN (Cowdrey et al., 2013; Kaye et al., 2013). For instance, among those with AN, (i) olfactory, visual, and taste cues are reliably rated as *less* pleasant than observed in healthy controls (HCs) (Cowdrey et al., 2013; Jiang et al., 2010); (ii) *negative* affect is reliably elevated after meals (Anderson et al., 2014); and (iii) food consumption is reported to be *aversive* rather than hedonic (Bruch, 1978; Bruch et al., 1994). However, altered reward responding extends beyond food‐specific contexts, suggesting potentially phenotypic perturbations in reward‐related processes. To that end, diminished hedonia and a reduced drive to pursue novelty and fun (Boehm et al., 2018; Harrison et al., 2014) are evident, alongside an unease in social and sexual relationships (Gonidakis et al., 2015; Pinheiro et al., 2010), which persists even after remission.

At the neurobiological level, structural abnormalities in the brain's reward circuitry have been observed in AN, which is evident in both gray matter structures and white matter fiber tracts. Reduced gray matter volume is evident in key nodes of the brain's reward circuit, including the ventral striatum and orbitofrontal cortex (OFC) (Frank et al., 2013; Titova et al., 2013), and aberrant connectivity of white matter tracts in reward systems has also been observed (Cha et al., 2016; Via et al., 2014). In white matter tracts connecting key reward circuit regions of the ventral tegmental area (VTA) and the nucleus accumbens (NAc), we previously found in adolescents with AN abnormal microstructure in the form of reduced neurite and myelin density and reduced orientation dispersion (Murray et al., 2023). Further, orientation dispersion in this tract—a measure of tract “fanning,” which, in general, is negatively correlated with fractional anisotropy (FA) (Zhang et al., 2012)—was associated with subjective reward responsiveness.

With regard to functional activity in the brain's reward circuit, mixed results have emerged from functional magnetic resonance imaging (fMRI) studies of reward‐related tasks to date. In the context of food cues, fMRI studies have generally noted diminished corticostriatal activity in AN (Brooks et al., 2011; Jiang et al., 2019), which extends to the taste, smell, and sight of palatable foods (Holsen et al., 2012; Jiang et al., 2019; McFadden et al., 2014; Oberndorfer et al., 2013). However, other studies suggest *hyperactivity* in reward‐related regions such as the ventral striatum (Cowdrey et al., 2011) and amygdala (Vocks et al., 2010) in response to palatable food cues, despite those with AN implicitly and explicitly stating “liking” and “wanting” these foods less than controls (Cowdrey et al., 2013). In concert, heightened activity in prefrontal regions including the medial prefrontal cortex and dorsolateral prefrontal cortex following exposure to palatable food cues has driven several hypotheses suggesting elevated top‐down inhibition of reward processing (Kerr et al., 2017; Uher et al., 2003; Uher et al., 2004).

Furthermore, studies assessing dopaminergic function—a critical neurotransmitter relating to reward learning and hedonic responding—suggest trait‐level abnormalities in those with AN. For instance, *reduced* concentrations of CSF homovanillic acid—a dopamine metabolite—have been found in those with AN, even after recovery (Kaye et al., 1999), and greater dopamine receptor availability has been noted in the ventral striatum of those with AN (Frank et al., 2005). In keeping with these data, aberrant neural response to hedonic cues extends beyond food cues. For instance, those with AN show abnormal corticostriatal activity in response to monetary rewards (Wagner et al., 2007), which accords with behavioral data illustrating a diminished predilection toward valuing and pursuing immediate monetary gain (Steinglass et al., 2017).

Paradoxically, those with AN describe dietary restriction and the hunger state as intensely rewarding (Kaye et al., 2013, 2009), raising the intriguing question of whether dimensions of reward processing are intact but have antonymic associations to those in healthy individuals. Relatedly, empirical data have demonstrated elevated ventral striatum activity following exposure to images of thin people (Fladung et al., 2010, 2013), and elevated OFC activity has been observed in response to low‐calorie foods, which is associated with fasting levels of acylated ghrelin (Holsen et al., 2014). These data may suggest that hunger could amplify the reward processing of low‐calorie foods.

In the context of these mixed multimodal results, the question of whether there exists a fundamental aberrancy in hedonic processes in AN remains of critical importance. However, several key gaps remain in our understanding of reward processes in AN. First, the capacity for de novo learning of hedonic associations in AN has been largely understudied. Ascertaining the integrity of appetitive learning systems in AN, for which an ongoing indifference to palatable food consumption often persists despite specialized treatments (Pike, 1998; Schebendach et al., 2012), is crucial. Moreover, the central goal of treatment across *all* treatment modalities is oriented toward enhancing the incentive salience of food cues, promoting approach behaviors, and facilitating greater food consumption. As such, elucidating the integrity of appetitive learning in AN, and its decay and reinstatement, will inform efforts to optimize patient outcomes by targeting the incentive salience of recovery‐congruent cues and food‐related approach behaviors.

To address this gap, our group recently developed an fMRI study protocol to leverage an appetitive Pavlovian conditioning paradigm to probe hedonic learning systems in AN (Murray et al., 2022). Specifically, we will interrogate the acquisition, extinction, spontaneous reinstatement, and recovery of associative reward learning to a disorder‐neutral and positively valenced cue. While appetitive conditioning studies frequently employ palatable food cues (i.e., chocolate, sucrose) as the unconditioned stimulus (US), the use of palatable tastants in AN population is problematic as it is conflated with the existing *aversive* associations to palatable food tastants. Disorder‐neutral, positively valenced USs are therefore warranted.

However, in further understanding the functionality of reward‐related processed in AN, the dopaminergic system is a potentially critical factor, considering both its potent role in reward learning processes (Keiflin & Janak, 2015; Wise, 2004) and its sensitivity to weight loss and food restriction (Frank et al., 2019). For instance, animal studies have illustrated that food restriction and weight loss drive a sensitization of brain reward pathways (Avena et al., 2008; Carr, 2007; Carr et al., 2003) and dopaminergic neuronal activity (Oinio et al., 2017). This adaptive sensitization of D1 and D2/D3 receptors in response to food restriction is thought to drive greater motivation to forage and seek food (Frank et al., 2019). In keeping, the dopamine‐mediated prediction error response is elevated in the NAc, head of the caudate, and insula in underweight adolescents with AN, although this appears to normalize upon weight restoration (DeGuzman et al., 2017).

Thus far, the methods used to interrogate the dopaminergic system in AN have been limited to positron emission tomography (PET) and single‐photon emission computed tomography (SPECT) studies. One novel method of indexing dopaminergic activity, which may be less acutely sensitive to food restriction and weight loss, is neuromelanin‐sensitive magnetic resonance imaging (NM‐MRI). Neuromelanin, which is a byproduct of dopamine and catecholamine synthesis, is found in dopaminergic neurons in the substantia nigra and in the noradrenergic neurons of the locus coeruleus (Graham, 1979). The oxidation of cytosolic dopamine, advanced by ferric iron, reacts with cytosolic proteins and is polymerized, which yields an undegradable iron–melanin–protein complex (Graham, 1979). Following macroautophagy and fusion with lysosomes, these neuromelanin organelles accumulate over the lifespan and are not subject to proteasome degradation (Graham, 1979). As such, neuromelanin is likely not acutely affected by acute weight loss and food restriction—which therefore offers a novel window into assessing the cumulative activity of the dopaminergic system in midbrain regions. Of relevance to AN, single‐unit recordings in response to both (i) food and (ii) conditional stimuli signaling food delivery have been observed in dopaminergic neurons in the substantia nigra (Ljungberg et al., 1992; Mirenowicz & Schultz, 1994, 1996), underscoring the role of nigrostriatal dopaminergic pathways in food‐related reward processing.

NM‐MRI leverages the highly paramagnetic nature of iron–neuromelanin complexes, utilizing reduced magnetization transfer and shortened T1 relaxation times to generate high signal intensities in brain regions containing neuromelanin (Sulzer et al., 2018). Evidence from a series of validation studies suggests that NM‐MRI is a reliable proxy for dopaminergic activity in the striatum (Cassidy et al., 2019). A meta‐analysis indicated that NM‐MRI may reliably delineate those with Parkinson's disease—a disorder characterized by abnormalities in dopaminergic processes—from those without and with 89% sensitivity and 83% specificity (Cho et al., 2021). Further, a meta‐analysis of studies in schizophrenia found elevated neuromelanin contrast‐to‐noise ratio (NM‐CNR) in the substantial nigra but not the locus coeruleus (Wieland et al., 2021). However, currently there are no published studies of NM‐MRI in those with AN—a disorder with noted perturbations in dopaminergic processes. Given the cumulative acquisition of neuromelanin in midbrain regions throughout the lifespan, the likelihood of acute changes in neuromelanin in response to starvation and weight loss among those with AN is low. However, whether alterations in dopaminergic synthesis—which can be indexed by NM‐MRI—are related to illness features and reward functioning in AN is an important question. Emerging evidence in broader psychiatry suggests that diminished neuromelanin may be evident in disorders of impulsivity (Cassidy et al., 2019). Moreover, studies of OCD—a disorder highly comorbid with AN—suggest that greater symptom severity and illness duration are independently linked to greater perturbations in midbrain neuromelanin (Pagliaccio et al., 2023). As such, the assessment of midbrain neuromelanin and both illness duration and symptom severity in AN—a disorder highly linked to dopaminergic perturbations and altered hedonic drive—is warranted.

With these considerations, we extended a recently developed multimodal Pavlovian appetitive conditioning study in underweight and weight‐restored AN (WRAN) (Murray et al., 2022), to include the assessment of midbrain neuromelanin in the substantia nigra. Specifically, in addition to indexing the acquisition, extinction, spontaneous reinstatement, and recovery of associative reward learning across multiple units of analyses including subjective experience (self‐report), physiology (heart rate deceleration and pupillary dilation), neural response (brain activity in reward systems), and white matter structural connectivity (from diffusion‐weighted MRI) (Murray et al., 2022), we will also undertake baseline NM‐MRI. In avoiding the use of any cues that may have already acquired a negative valence in those with AN (e.g., food cues), our appetitive conditioning paradigm (Murray et al., 2022) will employ positively valenced, socially rewarding yet symptom‐neutral infant laughter sounds at the US, which adolescents with AN typically rate positively (Murray et al., 2022). The study aims to assess (i) group differences in NM‐CNR in the substantia nigra pars compacta (SNpc) among underweight restricting‐type AN (AN‐R) patients, weight‐restored AN‐R (WRAN‐R) patients, and age‐matched HCs, (ii) assess the extent to which NM‐CNR in the SNpc accords with illness duration among those with AN, (iii) assess the extent to which NM‐CNR in the SNpc accords with blood oxygen level dependent (BOLD) activity in nodes of the reward circuit during the acquisition of positively valenced associations, (iv) assess the extent to which NM‐CNR in the SNpc accords with structural connectivity in the reward circuit, and (v) assess the relationship between NM‐CNR in the SNpc and self‐reported AN trait appetitive motivation. With empirical findings noting stable sex differences in associative learning, the proposed study will include only female participants.

We hypothesize that (1) compared to controls, those with both acute AN and WRAN will demonstrate reduced NM‐CNR in the SNpc; (2) NM‐CNR in the SNpc will be associated with illness duration in both the underweight (e.g., current illness duration to date) and WRAN (e.g., overall illness duration) groups, respectively; (3) there will be an association between NM‐CNR in the SNpc and subjective appetitive motivation on the behavioral activation scale (BAS) across participants; and (4) there will be an association between NM‐CNR in the SNpc and structural connectivity (as indexed by FA) between VTA/SNpc and the NAc across participants. Lastly, (5) we will undertake exploratory assessments of the concordance between NM‐CNR in the SNpc and BOLD response in the NAc and SNpc during the acquisition stage of our conditioning paradigm, without a priori hypotheses.

## MATERIALS AND METHODS

2

### Reproducibility

2.1

This study has been registered with ClinicalTrials.gov (NCT05531604), and upon completion of data collection, summary data will be made publicly available. In addition, data analytic scripts will be made available upon request to the corresponding author.

### Participants

2.2

In keeping with our parent study^47^, participants will be female adolescents and young adults (aged 12–22 years), who are (1) acute and underweight AN (*N* = 30), (2) WRAN (*N* = 30), and (3) age‐matched HCs (*N* = 30). All participants will undergo structural NM‐MRI, diffusion MRI, and fMRI during appetitive conditioning. Additional recruitment and assessment information, such as inclusion and exclusion criteria, are described in detail in Murray et al. (2022).

### Neuromelanin‐sensitive MRI

2.3

NM‐MRI will be acquired with a GE Discovery 3T scanner with a 32‐channel head coil. We will acquire two‐dimensional gradient response echo sequence with magnetization transfer contrast (2D GRE‐MT) (Plane = Oblique; repetition time [TR] = 284 ms; echo time [TE] = 4.1 ms; flip angle = 50°; in‐plane resolution = 0.43 × 0.43 mm^2^; partial brain coverage with field of view [FOV] = 512 × 512 mm; number of slices = 10; slice thickness = 2.5 mm; slice gap = 0 mm; MT offset = 1200 Hz; acquisition time = 08:01 min:s). The image slab will be oriented along the anterior commissure–posterior commissure line, with the top slice approximately 3 mm above the floor of the third ventricle to provide coverage of portions of the midbrain containing the SNpc. Three‐dimensional T1‐weighted images (MPRAGE; 0.8 mm^3^) using HCP Lifespan protocols (humanconnectome.org) will be acquired and used for registration. Both NM‐MRI and T1‐weighted images will be visually inspected for artifacts. Preprocessing of the NM‐MRI will be performed using steps that have previously been shown to have high test–retest reliability (Ljungberg et al., 1992). Specifically, preprocessing will be performed using the Advanced Normalization Tools (ANTs; http://stnava.github.io/ANTs/), which will consist of (1) brain extraction of the T1‐weighted image, (2) co‐registration of the NM‐MRI to the T1‐weighted image in native space, (3) spatial normalization of the T1‐weighted image to standard MNI space through nonlinear registration, (4) application of the estimated transformation (determined in step 3) to the NM‐MR image, and lastly (5) spatial smoothing of the normalized NM‐MRI image using a 1‐mm full‐width half‐maximum (FWHM) 3D Gaussian kernel. For each participant, a mask of the crus cerebri will be created by manual tracing of the NM‐MRI image in MNI space using the Seg3D software (www.seg3d.org).

### Diffusion MRI

2.4

Diffusion‐weighted images will be acquired with a single‐shot spin‐echo echo planar sequence (TR = 4100 ms, TE = 81.7 ms; flip angle = 90°; FOV = 140 × 140 mm; resolution = 1.7 mm^3^; *b* = 3000, 2000, 1000, and 500 seconds/mm^2^; number of slices = 81; number of directions = 102; acquisition time = 07:11 min:s) in the posterior‐to‐anterior direction. A shortened sequence (number of directions = 6) in the anterior‐to‐posterior direction will also be acquired, resulting in pairs of images with reversed phase‐encoding directions (distortions going in opposite directions) that will be utilized for EPI distortion correction. Diffusion MRI preprocessing will be performed using FMRIB's Software Library (FSL; www.fmrib.ox.ac.uk/fsl/). Preprocessing steps will involve using FSL's TOPUP and EDDY tools to estimate and correct the susceptibility‐induced off‐resonance field and correct eddy/current movements. Additional denoising steps such as outlier replacement (Andersson et al., 2017), slice‐to‐volume movement correction (Andersson et al., 2017), and susceptibility‐by‐movement correction (Andersson et al., 2018) will be applied. Bayesian estimation of diffusion parameters (BEDPOSTX) will be used to model and determine the number of crossing fibers per voxel (Jbabdi et al., 2012). Probabilistic tracking with crossing fibers (PROBTRACKX) (Behrens et al., 2007) will be estimated using VTA/SNpc as a seed region and NAc as the target region. Diffusion tensor model will be fitted using DTIFIT to derive FA maps and (exploratory) mean diffusivity (MD) and radial diffusivity (RD) maps.

### Outcome measures

2.5

#### Neuromelanin contrast‐to‐noise ratio

2.5.1

NM‐CNR will be calculated as the percent signal difference at each voxel relative to a participant‐specific reference of modal signal intensity in the crus cerebri, a nearby white matter region with minimal neuromelanin content (Cassidy et al., 2019). Average neuromelanin CNR will be extracted for the SNpc based on a probabilistic atlas (Ito et al., 2008).

#### fMRI BOLD signal

2.5.2

Acquisition and processing of the BOLD response will be performed as described in Murray et al. (2022). To explore the concordance between NM‐CNR in the SNpc and BOLD response in the NAc during the acquisition stage of our conditioning paradigm, probabilistic ROI of the NAc will be obtained using the Reinforcement Learning Atlas (Pauli et al., 2018).

#### Structural connectivity

2.5.3

The structural connectivity between the VTA/SNpc and the NAc will be determined as average FA (and as exploratory, MD, and RD) values of the right‐ and left‐averaged projection tract connecting the two regions.

### Data analysis

2.6

#### Analysis plan

2.6.1

Variable transformations prior to subsequent analyses will be determined based on distribution diagnostics and outlier analysis. To test Hypothesis 1, we will conduct an ANCOVA, controlling for age and pubertal development scale (PDS) scores, to compare mean NM‐CNR in the SNpc among AN, WRAN, and HCs. We will use multiple linear regression to test Hypothesis 2, examining associations between NM‐CNR in the SNpc and illness duration in the AN group, using age and PDS scores as covariates of noninterest. To test Hypothesis 3, we will use linear regression, examining associations between NM‐CNR in the SNpc and behavioral activation scale scores from the BIS/BAS across all participants, using age and PDS scores as covariates of noninterest. To test Hypothesis 4, we will use multiple linear regression to examine associations between NM‐CNR in the SNpc and structural connectivity (FA), controlling for age and PDS scores. For the exploratory analysis, we will use multivariate multiple linear regression to examine associations between NM‐CNR and BOLD signal. Dependent variables will be BOLD signal in the SNpc and the NAc from the CS+ versus CS− contrast (first eigenvariate) during the acquisition phase, and independent variables will be NM‐CNR in the SNpc, group (AN, WRAN, HCs), and group × NM‐CNR interaction, with age and PDS scores as covariates of noninterest.

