#### Power analysis

2.6.2

No published studies to date have assessed NM‐MRI in those with AN for estimates of effect sizes. As this is a secondary data analysis, the sample was powered for the primary outcomes for primary hypotheses of the parent study, as previously outlined (Murray et al., 2022). With a sample size of *n* = 30 AN, *n* = 30 WRAN, and *n* = 30 HCs, for Hypothesis 1, we will have power = .8 at alpha = .05 to detect an effect size of *f* = .33 (medium). For Hypothesis 2 (*n* = 30), we will have power = .8 at alpha = .05 to detect an effect size of *f*
^2 ^= .28 (medium). For Hypotheses 3 and 4 (*N* = 90), we will have power = .8 at alpha = .05 to detect an effect size of *f*
^2 ^= .089 (small).

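### The .8 power stated for Hypothesis 1 belongs to the three-group omnibus test, not to the claim that both AN and WRAN are reduced versus controls

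*Protocol article*

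**What the plan says.** The Introduction of the protocol article words Hypothesis 1 as directional and in two parts: "compared to controls, those with both acute AN and WRAN will demonstrate reduced NM‐CNR in the SNpc". Aim (i) in the same section is broader and asks only about differences among the three groups.

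Section 2.6.1 (Analysis plan) tests Hypothesis 1 with an ANCOVA "controlling for age and pubertal development scale (PDS) scores, to compare mean NM‐CNR in the SNpc among AN, WRAN, and HCs". It names no contrast of either patient group with HC, and no direction.

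Section 2.6.2 (Power analysis) attaches a figure to this hypothesis by name, at 30 per group: "for Hypothesis 1, we will have power = .8 at alpha = .05 to detect an effect size of *f* = .33 (medium"). The same section says that "the sample was powered for the primary outcomes for primary hypotheses of the parent study", and that there is no effect size to draw on: "No published studies to date have assessed NM‐MRI in those with AN for estimates of effect sizes". The figure is therefore a detectable effect at a fixed sample size, not a basis for choosing that size.

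**The concern.** A hypothesis that two groups are each below a control group is two directional comparisons, and it is supported only if both succeed. A three-group F asks a different question: whether the three means differ in any way. If the power given for Hypothesis 1 is the power of that F, it says nothing specific about showing a reduction in AN and a reduction in WRAN.

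Two things are at stake. A significant F could be reported as confirming reduced neuromelanin in both patient groups when it would be equally likely if WRAN were normal. And readers would take the study to have an 80% chance of supporting its first hypothesis at the stated effect, when under the same effect the chance is lower.

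**Working it through.** **Inputs.** n = 30 per group, N = 90, alpha = .05 and f = .33 (section 2.6.2); two covariates, age and pubertal score (section 2.6.1). Error df for the ANCOVA: 90 − 3 − 2 = 85. The article gives neither the pattern of means nor the sidedness of any contrast, so both are varied below.

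**Step 1: reproduce the stated figure.** Noncentrality λ = f² × N = .33² × 90 = 9.80.
- 2-df omnibus F: power .792 with 85 error df, or .793 with 87 (no covariates). The effect detectable with power .8 is f = .333. This matches the article.
- 1-df contrast with the same λ: power .872, detectable f = .299. This does not match.

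The article does not use the word omnibus, but its number identifies the test.

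**Step 2: turn f into differences from HC, in SD units.** f is the SD of the three group means divided by the within-group SD.
- AN and WRAN equally low (−d, −d, 0): f = d√2/3, so d = .33 × 3/√2 = .70.
- Only AN low (−d, 0, 0), or both raised (d, d, 0): same formula, d = .70.
- WRAN midway (−d, −d/2, 0): f = d/√6, so d = .33 × √6 = .81 for AN and .40 for WRAN.

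**Step 3: power of one contrast with HC.** The noncentrality of t is d × √(n/2). For d = .70 this is .70 × √15 = 2.71, which gives .76 (two-sided .05) or .85 (one-sided .05) on 85 df.

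**Step 4: power for both contrasts.** The two contrasts share the HC mean and the error variance, so they are correlated. Joint power was simulated with 400,000 replicates, counting only results in the predicted direction:

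| Pattern at f = .33 | Omnibus F rejects | Both significant, two-sided .05 each | Both significant, one-sided .05 each |
|---|---|---|---|
| AN and WRAN equally reduced | .79 | .64 | .76 |
| WRAN midway between AN and HC | .79 | .33 | .45 |
| Only AN reduced | .79 | .025 | .05 |
| Both raised | .79 | 0 | 0 |

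As a check on the first row, independent tests would give .764² = .58 and perfectly correlated tests .76; .64 lies between. With a Bonferroni level of .025 for each two-sided test, the first two rows become .52 and .23.

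**Step 5: detectable effects at power .8, n = 30 per group, two-sided .05, equal deficits.** One contrast: d = .73. Both contrasts: d = .82, which is f = .815 × √2/3 = .38. With one-sided .05 tests, both contrasts need d = .73.

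**The case against.** The article is a condensed account. Group contrasts, their sidedness and any multiplicity rule within a named ANCOVA may well sit in an analysis plan that is not shown, and their absence here would not by itself be an error. A three-group F also answers aim (i). The power sentence is arithmetically right: f measures overall dispersion of means, and the sentence never says that both contrasts will be significant with probability .8. No sample-size decision rests on it. The size of the shortfall depends on assumptions, and with one-sided tests and equal deficits joint power is .76, close to .8.

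Most of this stands. It rules out reading the article as having no follow-up comparisons or as having miscalculated. It does not remove the mismatch: section 2.6.2 assigns the figure to Hypothesis 1, the Introduction words that hypothesis as a reduction in both groups, and contrasts specified elsewhere would leave the stated .8 too high for it.

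A reader might go further and infer that the omnibus F wastes power and that pooled patients versus HC should be the main test, since the Introduction says that "neuromelanin is likely not acutely affected by acute weight loss and food restriction". The documents do not support this. That sentence does not say that AN and WRAN have equal means, and Hypothesis 2 links NM-CNR to illness duration, which may differ between the groups. The pooled contrast has power .87 under equal deficits, but if only AN is reduced the pooled difference is .70/2 = .35, its noncentrality is .35/√(1/60 + 1/30) = 1.57, and power falls to .34. Nor can it show that both groups are reduced. Requiring a significant F before the two contrasts costs almost nothing: joint power is .633 instead of .641 under equal deficits.

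**Conclusion.** The point holds as a mismatch between the hypothesis and the power attached to it. The f = .33 is correct as the detectable effect of the 2-df omnibus test. It is not the power for Hypothesis 1 as worded, because that test rejects equally often when the hypothesis is true, half true or reversed.

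At f = .33 the joint power is below .8 in every case tried: .64 (two-sided) or .76 (one-sided) under equal deficits, .33 or .45 with WRAN midway, and down to .23 with WRAN midway and a Bonferroni level. No single value should be cited as the true power, since the article fixes neither the pattern of means nor the sidedness. That the omnibus figure is not the power for a reduction in both groups depends on none of these assumptions.

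**What to change.** Within the same ANCOVA, name AN versus HC and WRAN versus HC as the planned contrasts for Hypothesis 1 and state their sidedness. Claim a reduction in both groups only if both contrasts are significant in the predicted direction. Because that claim requires both to succeed, it needs no split of alpha; if either group is also to be claimed alone, state the multiplicity rule. Keep the omnibus F as the test for aim (i).

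In section 2.6.2, label f = .33 as the detectable effect of the omnibus test, and add that with two-sided .05 tests the detectable effect at power .8 is d of about .73 for one contrast and about .82 for both, assuming equal deficits.

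The cost is a few sentences, best settled before the data are analysed, and a less favourable stated figure for the claim about both groups. The sample, fixed by the parent study, does not change.

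### Hypothesis 2 covers both the underweight AN and the WRAN groups, but the analysis plan tests it in the AN group only, so its WRAN half has no planned test

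*Protocol article*

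**What the plan says.** **Hypothesis (Introduction, last paragraph).** The prediction for midbrain neuromelanin contrast is that it "will be associated with illness duration in both the underweight (e.g., current illness duration to date) and WRAN (e.g., overall illness duration) groups, respectively". Two groups are named, and each has its own definition of duration.

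**Aim (ii) (Introduction).** The aim is to assess how far NM-CNR "accords with illness duration among those with AN". This does not say whether weight-restored patients are included.

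**Analysis (2.6.1).** Hypothesis 2 is tested by multiple linear regression, "examining associations between NM‐CNR in the SNpc and illness duration in the AN group", with age and PDS as covariates. The sentence before it, on Hypothesis 1, sets out "to compare mean NM‐CNR in the SNpc among AN, WRAN, and HCs", so AN and WRAN are separate labels in this section.

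**Power (2.6.2).** "With a sample size of *n* = 30 AN, *n* = 30 WRAN, and *n* = 30 HCs, for Hypothesis 1" gives the three group sizes. The next statement reads "For Hypothesis 2 (*n* = 30), we will have power = .8 at alpha = .05 to detect an effect size of", followed by the value f² = .28. It does not name the group to which the 30 refers.

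**The concern.** A numbered hypothesis makes a claim about two groups, and the only analysis assigned to it uses one. The separate definition of duration for WRAN shows that this group was a deliberate part of the claim.

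Followed as written, the study can neither support nor fail to support Hypothesis 2 in weight-restored patients. Any WRAN result on illness duration would be an unplanned analysis, or half of a stated hypothesis would go unreported. It would also remain open until after the data are seen whether the authors analyse AN alone, run two separate tests or pool the groups. These options answer different questions and have different power.

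**Working it through.** **1. Is there a WRAN duration test anywhere?** The models stated in 2.6.1 are:

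| Analysis | Sample | Illness duration in the model? |
|---|---|---|
| Hypothesis 1, ANCOVA | AN, WRAN, HC | No |
| Hypothesis 2, regression | AN group | Yes |
| Hypothesis 3, regression on BAS | All participants | No |
| Hypothesis 4, regression on FA | N = 90 (from 2.6.2) | No |
| Exploratory BOLD model | AN, WRAN, HC | No |

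Illness duration appears once, in a model restricted to AN.

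**2. Could the AN group mean all patients?** Section 2.6.1 lists AN, WRAN and HCs as three separate groups for Hypothesis 1 and again for the exploratory model. Section 2.6.2 gives n = 30 for Hypothesis 2, whereas all patients would be 30 + 30 = 60. The power figure gives a further check.

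**3. Reproducing the stated power.** Inputs from 2.6.1 and 2.6.2: n = 30, alpha = .05, f² = .28, and three predictors (duration, age, PDS), of which one is tested. The method is a noncentral F test of one coefficient:

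- λ = f² × N = .28 × 30 = 8.4
- df1 = 1; df2 = N − 3 − 1 = 26
- power = P[F(1, 26; λ = 8.4) exceeds the 95th percentile of the central F(1, 26)] = .797
- f² detectable at power .8 = .282

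This reproduces the stated .8 at f² = .28. Other readings do not: a one-sided test gives .88, and a 3-df test of the whole model gives .61.

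**4. The same calculation with N = 60.** With three to five predictors, the detectable f² at power .8 is .135 to .136. The stated .28 is therefore a figure for one group of 30, not for AN and WRAN pooled.

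**5. What a WRAN test would offer.** WRAN also has n = 30. With the same covariates, power at f² = .28 is again .797.

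**6. Consequences of the success rule, which the article does not state.** Assume independent tests in the two groups and, for the power figures, the same true f² = .28 in each.

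- Each group reported on its own at alpha = .05: power .797 per group.
- Both groups must be significant: .7967² = .635. Joint power of .8 needs √.8 = .894 per group, which requires f² = .371.
- Either group suffices, each at .05: chance of at least one false positive = 1 − .95² = .0975.
- Alpha split to .025 per group: power .697 per group, and f² = .350 is needed for .8.

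**The case against.** **Article format.** A journal article condenses a fuller plan, and a separate SAP might contain the WRAN model. That would excuse silence. Here the article does state the Hypothesis 2 analysis, and what it states conflicts with its own hypothesis.

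**The power statement.** A reader might infer that the power calculation also leaves out WRAN and that the stated .8 is wrong for Hypothesis 2. The documents do not support this. Section 2.6.2 says only n = 30 without naming a group, and WRAN is also 30. The hypothesis ends with a term meaning one association per group, which fits two separate regressions of 30 each. The figure is correct for each. It rules out a pooled analysis of 60 but does not exclude WRAN; only the wording of 2.6.1 does that.

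**Joint power of .63.** A reader might also infer that this is the true power for Hypothesis 2. It is so only if both groups must be significant, and the article adopts no such rule.

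**Pooling.** One model in 60 patients looks attractive because it detects about half the effect size (f² = .136). It is not a good replacement. Duration is defined differently in the two groups, and a common slope changes the question from each group to the average. Pooling only when the slopes do not differ significantly is also a weak safeguard. If f² is .28 in AN and zero in WRAN, with equal residual and duration variances, the slope-difference test has λ = .28 × 30 / 2 = 4.2 and power of only about .52 (df2 = 54). The groups would be pooled about half the time although WRAN has no association.

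**Importance.** This is a secondary analysis in a sample powered for the parent study. The gap leaves the other hypotheses untouched and biases no stated estimate. That limits its weight but does not remove it.

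**Conclusion.** The point holds as an inconsistency between the Introduction and section 2.6.1: one of the two groups named in Hypothesis 2, 30 of 60 patients, has no planned test. This rests on the article's wording alone and needs no numerical assumption.

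The stated power is correct for a single group (.797 recomputed against .8) and would hold equally for a WRAN regression. What 2.6.2 lacks is a statement of which test the figure describes and what counts as support for the hypothesis. The fall to about .63 is conditional on requiring both groups, with independent tests and equal effects.

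**What to change.** **In 2.6.1**, add a second regression of the same form in the WRAN group (n = 30), with overall illness duration as the predictor and age and PDS as covariates. Report both group-specific slopes with confidence intervals. Alternatively, restrict Hypothesis 2 in the Introduction to the underweight group. A pooled model in 60 patients may be added as a supplementary analysis but should not replace the group-specific tests.

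**In 2.6.2**, state that f² = .28 at power .8 applies to each group's own test at alpha = .05. Say whether support for Hypothesis 2 needs one group or both, and how alpha is handled. If both are required, give the joint power of about .63 at f² = .28 with its assumptions.

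**Cost.** One extra model, a few words in two sections, and a second test at alpha = .05. No extra participants or scans are needed, because 30 WRAN participants are already planned for NM-MRI and the hypothesis presupposes that their illness duration is recorded. The article describes data collection as still to be completed, so the change should be recorded before the analysis begins.
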